#### Body Exposure Sessions

The four computer based body exposure sessions are identical and involve a guided exposure to the previously taken photographs of the participant's own body on the computer screen. Standardized instructions are played to the participants via audio file and reactions and short descriptions of their body parts will be supervised by the study attendant who is present during the sessions. In the beginning and at the end of each session, there is a 30 s period of free viewing time for each the frontal and lateral photograph. During this time, participants are viewing the pictures without any instruction and eye movements are recorded in order to measure AB. The audio file guides participants in viewing their own bodies on the computer screen for an overall duration of about 30 min. The body exposure follows an adapted version of the manualized treatment program by Vocks and Legenbauer (62), in which participants are guided to look at 12 body parts following a fixed sequence. To assess stress reactivity, four saliva samples are taken before, during directly after and 30 min after the end of the body exposure with emotions being rated at the same times. Heart rate variability will be assessed continuously throughout each session via heart rate monitor. The standardized procedure of a body exposure session is shown in Figure 2.

**Figure 2 F2:**
[figure not shown]
Standardized procedure of an exposure session with attentional bias (AB) assessments (1,2) for each frontal and lateral view (30 s each), stress measurements (1-4) via emotion ratings and saliva samples, guided body exposure times (1,2), and heart rate sampling (from AB Assessment 1 to Stress 3).

#### Post-intervention Session

During the post-intervention session, participants are again asked to complete questionnaires, including the EDI-2, the BIAQ, the BCQ, and the attractiveness ratings of the body parts. For the AN-TAU group, AB is assessed again during this session.

### Data Analysis

Research questions will be analyzed in repeated measures (rm)-AN(C)OVAs, considering within-subject and between-subject factors and interpreting—depending on the respective hypothesis—main and/or interaction effects. To test intervention effects on body dissatisfaction, body control and body avoidance, as well as AB comparing AN-INT vs. AN-TAU within the RCT, a 2 × 2-rm-AN(C)OVA (between-subject factor = group: AN-INT vs. AN-TAU; within-subject factor = time: pre, post) will be conducted. To assess modifications within and throughout the body exposure sessions regarding AB, emotion ratings, HR, HRV, as well as cortisol and sAA reactivity slope, a 2 × 4-rm-AN(C)OVA (between-subject factor = group: AN-INT vs. CG-INT; within-subject factor = time: 4 exposure sessions) will be conducted. Potential confounders are derived from a theoretical point of view (e.g., age, depression) and will be included as covariates in the statistical analyses (ANCOVAs). Specific test requirements will be tested prior to performing the full analysis. In case of non-adherence to the test requirements (i.e., normal distribution and variance homogeneity), the outcome measures will be logarithmized and additional non-parametric tests will be calculated. Data will be analyzed using IBM SPSS Statistics software. Significance level will be set at *p* =.05 and effect sizes will be interpreted. Effect sizes for AN(C)OVA results were computed as partial η^2^ ($\eta_{\text{p}}^{2}$), with values $\eta_{\text{p}}^{2}$ <0.06 interpreted as small,.06 ≤ $\eta_{\text{p}}^{2}$ <0.14 as medium and $\eta_{\text{p}}^{2}$ ≥ 0.14 as large effects (64). Correction for multiple testing will be applied if necessary.

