## Objectives

Due to the high association of BI disturbances and the development and maintenance of EDs, including AN, psychotherapy with patients with AN in any setting should include modules treating body image disturbances explicitly (8). A need for new, emerging treatments with a focus on brain-based interventions as well as mechanism-based approaches, which are specifically addressing psychopathology and BI disturbances, have been proclaimed (43, 44). While there is data available on the efficacy of body exposure interventions for reducing BI disturbances in women with EDs and high body dissatisfaction (20, 25), there is a lack of available data regarding the efficacy of body exposures with children and adolescents. Furthermore, different EDs are frequently mixed up in the literature, making it difficult to investigate specific processes, which might differentiate between body dissatisfied individuals with EDs and body dissatisfied individuals without EDs. Also, underlying psychophysiological and neurobiological processes during body exposure are still poorly understood. Therefore, the aim of this study is to investigate the short-term efficacy of a computer-based body exposure intervention for adolescents with AN. This group is being compared to an AN-TAU group and a body dissatisfied clinical control group.

The primary research question is: Is body dissatisfaction in adolescents with AN reduced after completing a four-session computer based body exposure intervention, compared to TAU?

Secondary research questions include: (1) Body checking and avoidance: Can four sessions of a computer based body exposure intervention reduce body checking and body avoidance behavior, compared to TAU? (2) Viewing patterns / attentional bias (AB): Can the AB in terms of focusing more on negatively rated body parts, measured via eye tracking, be reduced by a four-session computer based intervention in adolescents with AN, compared to TAU? Are there AN-specific AB modifications in comparison to a body dissatisfied control group also obtaining the intervention? (3) Stress reactivity: Do four sessions of body exposure modify stress reactivity in terms of a physiological habituation, measured via salivary cortisol, sAA, HR and HRV? Are there AN-specific effects in physiological habituation in comparison to a body dissatisfied clinical control group?

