Until now and to the best of our knowledge, no study using a comparable computer based body exposure intervention using photographs of the own body could be identified. Because of this, sample size calculation for the current pilot study was performed in accordance with former studies assessing effects of mirror (body) exposure in adolescents and adults with EDs (23, 42), as well as fear-stimulus exposure in phobic adolescents (48), reporting mostly medium effect sizes for body avoidance (body) anxiety and negative emotions. According to sample size calculations [G^*^Power; (49)] based on default values (alpha error =.05, power =.80) and the assumption that effect sizes for the RCT (AN-INT vs. AN-TAU) are expected to be larger than for the comparison of AN-INT vs. CG-INT, both taking part in the same intervention, at least 23 participants are required for the intervention groups (AN-INT, CG-INT) and at least 15 participants are required for AN-TAU. This is calculated based on a 2 × 2-mixed design (RCT; between-subject factor: AN-INT vs. AN-TAU; repeated measure within-subject factor: pre, post) and a 2 × 4-mixed design (AN-INT vs. CG-INT; repeated measure within-subject factor: 4 exposure sessions), respectively.

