## Strengths and Expected Outcomes

The multi-level approach of this study allows for both an objective and a subjective evaluation of the short-term effects of the proposed computer based body exposure intervention. It will give new insights into the effects and underlying processes of the underresearched field of body exposure in adolescents with AN. The collected data will be assessing different aspects of body dissatisfaction and general psychopathology by employing questionnaires, measuring AB, utilizing emotion ratings, recording HR and HRV, as well as determining salivary cortisol and sAA levels, throughout the exposure sessions. Besides comparing the pre-post intervention effect with TAU within an RCT, this study will also investigate how the processes that underlie body exposure change throughout the intervention and if there are AN-specific modifications in comparison to adolescents with high body dissatisfaction (CG-INT). Corresponding with the current literature regarding body exposure interventions, especially for adolescents with AN, we expect psychopathology (body dissatisfaction, body image avoidance, body checking) to be reduced at the end of the intervention compared to the beginning of the intervention and with TAU and the AB to weaken (shown by spending less time looking at the negatively rated body parts). Furthermore, we expect a physiological habituation, both within and across sessions, with a decrease in emotion ratings, HR and neuroendocrine stress levels. To put it in a nutshell, results of this pilot study will give new insights into the effectiveness of and the processes underlying body exposure interventions in children, adolescents, and young women. Despite a relatively small sample size, a comprehensive in-depth analysis, implemented by multi-level assessment, will be carried out, thereby expanding the so far weak literature on mechanisms of BI disturbances and specific interventions for the abovementioned patient groups. The results of the current pilot study will be used for the design of a subsequent larger, multi-center intervention study with adolescents with AN, helping e.g., to identify modifiable BI and psychopathologic outcome measures, to select relevant and modifiable stress markers, and to provide orientation toward expectable effect sizes.

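### The randomised comparison puts the baseline score in the time factor of a 2 × 2 repeated-measures model; baseline-adjusted ANCOVA would give a modest, nearly free gain in precision

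*Protocol article*

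**What the plan says.** The Objectives section asks a randomised question: "Is body dissatisfaction in adolescents with AN reduced after completing a four-session computer based body exposure intervention, compared to TAU". The Data Analysis section answers it with a 2 × 2 repeated-measures AN(C)OVA ("between-subject factor = group: AN-INT vs. AN-TAU; within-subject factor = time: pre, post"), used also for body checking, body avoidance and attentional bias (AB).

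Two further sentences in Data Analysis matter. One, covering all research questions, says how effects will be read: "interpreting—depending on the respective hypothesis—main and/or interaction effects". The other concerns covariates: "Potential confounders are derived from a theoretical point of view (e.g., age, depression) and will be included as covariates". The baseline value of the outcome is not among the examples.

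The Strengths and Expected Outcomes section expects psychopathology "to be reduced at the end of the intervention compared to the beginning of the intervention and with TAU". The Target/Study Population section bases the sample size on the same 2 × 2 design: "at least 23 participants are required for the intervention groups (AN-INT, CG-INT) and at least 15 participants are required for AN-TAU".

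**The concern.** Randomised arms share one expected baseline mean, so any observed baseline difference between them is chance. At 23 against 15 that difference has a standard error of 0.33 SD, so about one trial in three starts more than 0.33 SD apart. A change score subtracts the baseline with a coefficient of 1, which over-corrects for such imbalance whenever ρ is below 1. ANCOVA estimates the coefficient and so gives a more precise treatment effect from the same data. With 38 randomised patients this is worth having.

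The article also does not say in so many words which of the three F-tests of the 2 × 2 model answers the primary question. The results are meant to guide effect-size expectations for a later multi-centre trial, so the term that is reported should be unmistakable.

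**Working it through.** **The plan's own figure.** The article gives "default values (alpha error =.05, power =.80") and describes the earlier studies as "reporting mostly medium effect sizes for body avoidance (body) anxiety and negative emotions". It states no numerical effect size, no correlation and no tested effect, so the 23 and 15 cannot be strictly reproduced. As an illustration, f = 0.25 and ρ = 0.5 for the interaction need 34 patients in total in the 2 × 2 design. At ρ = 0.5, the planned 38 correspond to f = 0.234. This only shows that the effect size and ρ below have to be assumed.

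**Inputs.** From the article: n = 23 and 15, alpha 0.05 (taken as two-sided). Assumed: a true post-intervention difference d of 0.8 SD or 0.5 SD, equal SDs at pre and post, and ρ from 0.5 to 0.8.

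**Formulas, in units of the outcome variance.** Let k = 1/23 + 1/15 = 0.1101, so √k = 0.332.

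- Interaction (change score): variance factor 2(1−ρ), 36 df.
- ANCOVA: variance factor 1−ρ², 35 df. Estimating the slope inflates this on average by 1 + 1/34 = 1.029.
- Ratio before the inflation: (1−ρ²) / [2(1−ρ)] = (1+ρ)/2, that is 0.75, 0.85 and 0.90 at ρ = 0.5, 0.7 and 0.8.
- Noncentrality: d / √(variance factor × k), referred to the noncentral t distribution.

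**Example, d = 0.8 and ρ = 0.5.**

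- Interaction: 0.8 / (√1.0 × 0.332) = 2.41, power 0.65.
- ANCOVA: 0.75 × 1.029 = 0.772, and 0.8 / (√0.772 × 0.332) = 2.74, power 0.76.

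| d | ρ | Interaction | ANCOVA |
|---|---|---|---|
| 0.8 | 0.5 | 0.65 | 0.76 |
| 0.8 | 0.7 | 0.86 | 0.90 |
| 0.8 | 0.8 | 0.96 | 0.97 |
| 0.5 | 0.5 | 0.31 | 0.39 |
| 0.5 | 0.7 | 0.47 | 0.52 |
| 0.5 | 0.8 | 0.64 | 0.67 |

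Simulation of 40,000 trials per setting agrees to within 0.01, and both tests keep their 5% level when the arms do not differ. At ρ = 0.9 the two are practically equal.

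**The main effects of the same model.**

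- Group: it averages pre and post, so it carries d/2 with variance factor (1+ρ)/2. At d = 0.8 its power is 0.27 at ρ = 0.5 and 0.25 at ρ = 0.7.
- Time: it pools the arms. If both improve by 0.5 SD of the change score and do not differ (an assumption), it is significant in about 83% of trials.

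Neither estimates the effect against TAU.

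**The case against.** The strongest reply is that the planned test is sound. In a randomised pre-post design the group × time interaction is unbiased and holds its level. This stands: the model is inefficient, not wrong.

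A reader might infer that the plan intends to read a time or group main effect as the effect of the intervention. The documents do not support that. The sentence on main and interaction effects covers every research question, including the 2 × 4 habituation analyses, where a main effect of time is a legitimate target, and it ties the choice to each hypothesis. The primary question is framed against TAU, and Strengths and Expected Outcomes describes the randomised contrast as a comparison of the pre-post effect with TAU, which is the interaction. A main-effect reading is left possible by the wording but is not announced. The group main effect is also still a randomised contrast at its nominal level; it is diluted, not biased under the null.

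A further reply is that AN(C)OVA with an open covariate list may already include the baseline score. It may: adding that score as a covariate would make the group × time test equal to ANCOVA. But the article names only theory-derived confounders, with age and depression as examples, and places the pre score in the time factor.

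Finally, the gain depends on ρ. The questionnaires are repeated within about 2.5 weeks, so a high ρ is plausible, and the gain is then small. This stands too.

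**Conclusion.** The point holds as an efficiency improvement, not as an error. As written, the randomised comparison amounts to a change-score test, and adjusting for a baseline score that is already collected would be more precise. Under an assumed difference of 0.8 SD the gain is about 11 power points at ρ = 0.5, 4 at ρ = 0.7 and 1 at ρ = 0.8; for 0.5 SD it is about 8, 5 and 3. These figures rest on d and ρ, neither of which the article states, and on equal SDs at pre and post. The remark on main effects is a request for clarification only.

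**What to change.** State in Data Analysis that the primary analysis is ANCOVA of post-intervention EDI-2 body dissatisfaction on arm (AN-INT against AN-TAU), with pre-intervention EDI-2 body dissatisfaction as covariate, reported as the adjusted mean difference with its 95% confidence interval. Use the same model for the BIAQ and BCQ, each with its own pre score. Add one sentence that neither the time nor the group main effect of the 2 × 2 model is read as the effect against TAU.

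Do not carry the model over to AB as a matter of wording. The Procedure section describes AB recordings at the pre- and post-intervention sessions for AN-TAU but within the exposure sessions for the intervention groups. Pre and post AB would first have to come from comparable occasions in both arms.

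The cost is one degree of freedom and a few lines of text. The EDI-2, BIAQ and BCQ are already completed before and after the intervention, and no additional patients are needed.

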While investigating stress reactivity to body exposure in women with BN who obtained six therapeutic sessions of ME, a decrease of salivary cortisol levels from the initial to the final intervention session was observed; this could be interpreted as habituation of the neuroendocrine stress response (40). Furthermore, a study in women with binge eating disorder found interactions between induced stress and body dissatisfaction during ME by measuring the biological response to social stress via salivary cortisol and sAA (41). Additionally, ED patients showed higher cortisol levels than control participants during a single 40-min body exposure task in a study exploring neuroendocrine (salivary cortisol) and physiological (skin conductance, heart rate) responses in women with EDs, compared to healthy controls. However, no group differences regarding neuroendocrine or physiological reactivity occurred (42). Investigating the effect of a three-session mirror exposure on psychophysiological sympathetic reactivity (HR, HRV, skin conductance) in women with BN vs. healthy controls showed an initial response within the sessions in both groups, but no physiological habituation between the sessions; thereby, the initial response was an unexpected decreasing sympathetic activity which might be explained by the stronger feelings of sadness compared to fear (28). So, until now, exact physiological mechanisms which go along with repeated body exposure in patients with AN or high body dissatisfaction are not yet clarified, with no study, to the authors' knowledge, investigating these in adolescents.

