Stress levels and stress reactivity are assessed through multiple measures. Firstly, subjective emotion ratings (anxiety, anger, disgust, stress, and sadness) are obtained on a ten-point Likert scale before, during, directly after, and 30 min after each exposure session. Secondly, participants' cardiac activity is monitored during the exposure sessions using a Scosche^®^ Rhythm 24 Heart Rate monitor. Raw data is further processed using Python (https://www.python.org/). RR intervals (RRI) will be detected by a peak-detection algorithm and outliers will be removed using implemented python libraries (e.g., hrv-analysis 1.0.4 package). Instantaneous heart rate (IHR), as a measurement of heart rate variability (HRV), will be derived following IHR$=\frac{60000}{RRI}$, where RRI are measured in milliseconds (61). Changes in HR/IHR and RRI in relation to the number of exposure sessions, i.e., changes over the course of the four exposure sessions, will be analyzed. Thirdly, saliva samples are taken before, during (10 min into the exposure), directly after and 30 min after the body exposure using Salivettes^®^ (Sarstedt, Nümbrecht, Germany). Cortisol, as well as sAA, levels are subsequently analyzed in the laboratory. To do this, saliva samples are stored at −20°C until processing. When processing begins, the samples are thawed and centrifuged at 2,000 × g and 20°C for 10 min. To analyze salivary free cortisol, a commercial chemiluminescence immunoassay (CLIA; IBL Hamburg, Germany) is used, following the manufacturer's instructions. Similarly, to measure sAA, a quantitative enzyme kinetic method is employed, following a standardized protocol.

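### Across-session habituation is expected as falling cortisol and sAA levels, but the only variable named for the 2 × 4 model is a within-session reactivity slope, which cannot show a uniform fall in level

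*Protocol article*

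**What the plan says.** All references are to the protocol article.

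- **Objectives, secondary question 3** is worded as reactivity: "Do four sessions of body exposure modify stress reactivity in terms of a physiological habituation, measured via salivary cortisol, sAA, HR and HRV".
- **Strengths and Expected Outcomes** words the expectation as levels: "we expect a physiological habituation, both within and across sessions, with a decrease in emotion ratings, HR and neuroendocrine stress levels".
- **Introduction** cites, from women with bulimia nervosa, a precedent that is also about levels: "a decrease of salivary cortisol levels from the initial to the final intervention session was observed; this could be interpreted as habituation".
- **Parameters** fixes four samples per session: "saliva samples are taken before, during (10 min into the exposure), directly after and 30 min after the body exposure". **Body Exposure Sessions** repeats the four times, "with emotions being rated at the same times".
- **Data Analysis** names the variables for the AN-INT versus CG-INT model, "regarding AB, emotion ratings, HR, HRV, as well as cortisol and sAA reactivity slope", with "within-subject factor = time: 4 exposure sessions".

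In that last list only cortisol and sAA are reduced to a slope. Emotion ratings, HR and HRV are not. No formula for the slope is given, and no level, area or pre-exposure value is named for either hormone marker.

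**The concern.** The article states both an expectation and the variable to be analysed, and the two differ. A slope describes the shape of the response within a session. A fall in level between sessions is a different quantity, and a participant can show either without the other.

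Two consequences follow. First, if cortisol or sAA falls evenly from session 1 to session 4, as the expectation and the cited precedent suggest, the named analysis may find nothing. Second, from session 2 on the participant knows what is coming. If the sample taken before the exposure rises for that reason, a slope that uses this sample becomes flatter although she is no less stressed.

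Habituation is the mechanism that the abstract sets out to investigate. The results are also meant to help select modifiable stress markers and to indicate effect sizes for a larger multi-center study. A slope read alone could lead to a marker being kept or dropped for the wrong reason.

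**Working it through.** **Inputs.** From the article: four samples per session (before, 10 min in, directly after, 30 min after), about 30 min of guided viewing, and 23 participants in each intervention group. This places the samples at roughly 0, 10, 30 and 60 min. The article gives no hormone means, standard deviations or correlations, so there is no hormone figure to reproduce and all values below are assumed. The point does not depend on the sample size calculation.

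**Step 1. What a slope can and cannot see.** Assumed reference profile: 5, 6, 8, 6.5 (arbitrary units).

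- Rise = directly after − before = 8 − 5 = 3.0.
- Least-squares slope b = Σ(t − t̄)(y − ȳ) / Σ(t − t̄)². With t̄ = 25 this is 52.5 / 2100 = 0.025 per min, or 1.50 per 60 min.
- Area with respect to ground (trapezoid) = 55 + 140 + 217.5 = 412.5.

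| Change from reference | Rise | Slope per 60 min | During to after | Mean | Area |
|---|---|---|---|---|---|
| None | 3.0 | 1.50 | 2.0 | 6.375 | 412.5 |
| All samples −1 | 3.0 | 1.50 | 2.0 | 5.375 | 352.5 |
| All samples −2 | 3.0 | 1.50 | 2.0 | 4.375 | 292.5 |
| Before +0.5 | 2.5 | 1.14 | 2.0 | 6.50 | 415.0 |
| Before +1.0 | 2.0 | 0.79 | 2.0 | 6.625 | 417.5 |
| Before +1.5 | 1.5 | 0.43 | 2.0 | 6.75 | 420.0 |

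*Uniform fall.* A constant cancels from any difference or slope, whichever samples enter it. The area falls by 60/412.5 = 14.5% and 120/412.5 = 29.1%, and the slopes do not move. The log transformation that Data Analysis holds in reserve does not solve this: on the log scale a uniform proportional fall is the constant that cancels. On the raw scale a proportional fall does shrink the slope (a 20% fall takes the rise from 3.0 to 2.4), but the result then mixes lower level with lower reactivity.

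*Rise in the pre-exposure sample only.* The rise shrinks by up to half and the four-point slope by up to 71% (1.50 to 0.43), while the mean increases by 5.9%. The during-to-after change stays at 2.0, so the effect depends on the slope's definition. The area moves by only 7.5/412.5 = 1.8%, because the first sample carries 5 of the 60 min. The area alone would therefore not reveal anticipation, and the pre-exposure sample has to be examined separately.

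**Step 2. Could this reach significance at the planned size?** Simulation of the 2 × 4 repeated-measures ANOVA: 2 × 23 participants, 2000 runs per setting, unit-SD samples, within-session correlation 0.5 or 0.7. Only the pre-exposure mean rises, linearly over the four sessions; the post-exposure mean is constant. The outcome is post minus pre, and the test is the time effect at 0.05.

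| Total rise in pre-exposure mean | Significant time effect, post − pre | Same test, post-exposure level |
|---|---|---|
| 0 | 5–6% | 5% |
| 0.25 SD | 18–24% | 5% |
| 0.5 SD | 54–76% | 5–6% |
| 0.75 SD | 90–99% | 5% |
| 1 SD | over 99% | 4–6% |

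This concerns the time effect. A rise in anticipation that is equal in both groups cancels from the group × time interaction; an unequal one does not. AN-TAU attends only the pre- and post-intervention sessions, so the across-session change has no unexposed comparator.

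**The case against.** The strongest objection is that the slope answers the question actually posed. Secondary question 3 asks whether the sessions modify stress reactivity, and a reactivity slope compared over four sessions does that. This stands: the slope is a legitimate outcome and should stay. It does not remove the mismatch, because the article also states an expectation about levels and names nothing that tests it.

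A reader might infer that the slope is anchored on each session's own pre-exposure sample, so that rising anticipation would be reported as habituation. The document does not support that. Anchoring is the natural reading of reactivity, but it is not stated, and a full plan that is not shown may define the slope differently. The misreading also needs anticipation to rise while later samples stay put. Emotion ratings are taken before each exposure and could reveal it, and nothing says the slope will be read alone. The opposite pattern, nervousness that raises only the first session's pre-exposure sample, would mask habituation instead. No direction of bias is established.

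A reader might also infer that a resting saliva sample at the pre-intervention session is needed as a common reference. It would not help. Saliva collection is introduced at the end of that session, after the body-part ratings and the photographs, so the sample would hardly be stress-free. A single reference value per participant also cancels from the time and group × time effects. A rule that accepts a flatter slope as habituation only if the pre-exposure sample has not risen is no better: with 46 participants, a non-significant rise does not show that there was none.

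**Conclusion.** The point holds as a mismatch between the stated expectation (levels) and the only cortisol and sAA variable named for the 2 × 4 model (slope). That no within-session slope can show a uniform fall in level on the scale analysed is a matter of algebra and needs no assumed values.

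The risk of misreading anticipation as habituation is conditional. It requires that the slope includes the pre-exposure sample and that this sample rises over sessions while later ones do not. Under the assumed simulation inputs, a rise of 0.5 SD is enough for a significant time effect in about 54–76% of runs. The likelihood of such a rise in this trial cannot be judged from the article.

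This is a secondary, mechanistic question in a pilot study. The primary comparison of body dissatisfaction with TAU is unaffected. The change is a worthwhile and inexpensive improvement, not a correction of an invalid endpoint.

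**What to change.** In Data Analysis, keep the reactivity slope and state which of the four samples enter it. In the same 2 × 4 model, add for cortisol and for sAA:

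1. the per-session overall level, for example the area under the curve with respect to ground, as the test of the expectation in Strengths and Expected Outcomes;
2. the pre-exposure sample, as a check on anticipation.

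State that a flatter slope will be interpreted together with both and with the pre-exposure emotion ratings, and word the expectation so that reactivity and level are named separately.

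No further saliva samples or visits are needed. The cost is two more secondary outcomes per marker (2 × 2 = 4 in all), to be placed under the multiplicity correction that Data Analysis already foresees, and possibly a less clear-cut reading if level and slope disagree.

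### Unless age and depression are centred, the session/time main effects of the planned SPSS repeated-measures ANCOVAs refer to a participant aged 0; group × time tests are unaffected

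*Protocol article*

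**What the plan says.** In the protocol article, Data Analysis names the model for the session outcomes (attentional bias, emotion ratings, HR, HRV, cortisol and sAA): "a 2 × 4-rm-AN(C)OVA (between-subject factor = group: AN-INT vs. CG-INT; within-subject factor = time: 4 exposure sessions". The pre/post outcomes of the randomised comparison get a 2 × 2 model of the same kind. Main effects, interactions or both are to be interpreted, depending on the hypothesis. On covariates it says "Potential confounders are derived from a theoretical point of view (e.g., age, depression) and will be included as covariates in the statistical analyses (ANCOVAs", and on software "Data will be analyzed using IBM SPSS Statistics software". Centring is not mentioned, and neither the SPSS procedure nor its syntax is given.

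Habituation is a stated hypothesis. Under Strengths and Expected Outcomes: "we expect a physiological habituation, both within and across sessions". Objectives asks first whether four sessions change stress reactivity, and only then whether the change is specific to AN. Target/Study Population sets the age range at 10 to 21 years, and Parameters gives the BDI-II as the depression measure.

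**The concern.** In a repeated-measures GLM each session contrast is regressed on an intercept, group and the covariates. The within-subject main effect is the test of that intercept, so it is the expected change when every covariate equals zero. With age in years, that is an extrapolation far below the youngest eligible participant.

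This matters because the first habituation question has no other natural test in the planned models. Under Design, AN-TAU completes only the pre and post sessions, so the randomised contrast cannot address change over the four exposures. Real habituation could be reported as absent. The article also uses partial η² bands to grade effects, and says the pilot will help select stress markers and give expected effect sizes for a larger trial. A responsive marker could be dropped because its partial η² was computed at the wrong covariate value.

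**Working it through.** **The plan's own figure.** Target/Study Population gives "alpha error =.05, power =.80", then "at least 23 participants are required for the intervention groups (AN-INT, CG-INT") and "at least 15 participants are required for AN-TAU". The effect size appears only in words ("reporting mostly medium effect sizes for body avoidance (body) anxiety and negative emotions") and no correlation between repeated measures is given, so the sample sizes can only be back-solved. For the 2 × 4 design with N = 23 + 23 = 46, and assuming a correlation of 0.5, power 0.80 corresponds to Cohen's f ≈ 0.175 (0.207 at correlation 0.3, 0.135 at 0.7).

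**Inputs.**
- From the article: n = 23 + 23, four sessions, α = 0.05, ages 10–21.
- Assumed, because the article gives none: age mean 16, SD 2.2 or 3.2; depression mean 20, SD 10; covariates uncorrelated; a linear session contrast with SD 1 and true mean decline d = 0.5.

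**Standard error.** With centred covariates, SE ≈ σ/√N. With uncentred covariates it is multiplied by about √(1 + (mean age/SD age)² + (mean depression/SD depression)²).
- Age SD 2.2: √(1 + 52.9 + 4) = 7.6.
- Age SD 3.2: √(1 + 25 + 4) = 5.5.

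Age contributes most of this: 52.9 of 57.9, or 25 of 30.

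**Power for d = 0.5.** The noncentrality is 0.5 × √46 = 3.39 when centred. Uncentred it is 3.39/7.6 = 0.45 or 3.39/5.5 = 0.62. On 46 − 4 = 42 degrees of freedom, a two-sided 5% t test has these powers:

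| Age SD | Centred | Uncentred |
|---|---|---|
| 2.2 | 0.91 | 0.07 |
| 3.2 | 0.91 | 0.09 |

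Simulations of the same set-up gave 0.91–0.92 centred and 0.06–0.10 uncentred. With age SD 2.2, uncentred power was only about 0.06 at d = 0.3 and 0.11 at d = 0.8 (centred 0.52 and 1.00).

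**Full four-session F test.** A separate simulation used the 3-df session test with age mean 15.5, SD 2 or 3, and depression 20 (SD 12) or 25 (SD 10):

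| Cohen's f | No covariates | Centred | Uncentred |
|---|---|---|---|
| 0 (true null) | 0.05–0.06 | 0.05 | 0.05–0.06 |
| 0.175 | 0.80–0.81 | 0.80–0.81 | 0.05–0.07 |
| 0.25 | 0.98–0.99 | 0.98–0.99 | 0.07–0.09 |
| 0.40 | 1.00 | 1.00 | 0.11–0.16 |

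**Partial η².** At d = 0.5 and age SD 2.2, the simulated median is about 0.22 centred and 0.01 uncentred. In the article's bands that is large against small. A hand check of the centred value: 3.39²/(3.39² + 42) = 0.21.

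**If habituation depends on age.** Suppose the decline is larger by 0.3 SD per SD of age. At age 0, which is 16/2.2 = 7.27 SDs below the mean, the model implies a decline of 0.5 − 0.3 × 7.27 = −1.68, that is, a rise. The noncentrality is then −1.68 × √46/7.6 ≈ −1.5. In simulation the uncentred test was significant in the wrong direction in 28% of trials, while the centred test kept power 0.90.

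**Group × time.** Centring only moves the intercept, so the group coefficient in each contrast regression is unchanged. In a simulated scenario with a true interaction, power was 0.776 both ways.

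**The case against.** The strongest reply is that the article never says the covariates go in uncentred. An analyst who centres them follows the text exactly, and covariate scaling is the kind of detail an article may leave to a fuller plan. This stands: a reader might infer that the plan prescribes a test at age 0, and the text does not support that. The low power figures follow from one way of carrying out the plan.

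Other parts of the reply also stand:
- The covariates are given as examples, and the AN(C)OVA notation leaves covariate-free models open.
- SPSS evaluates estimated marginal means at the covariate means by default, so an analyst reading those would not be misled. The problem sits in the omnibus test and its partial η².
- A BDI-II score of 0 is attainable; only the age origin lies outside the sample.
- Type I error stays near 0.05.

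A reader might also infer that the trial's main result is at risk. It is not: the primary question compares AN-INT with AN-TAU and is tested by group × time, as is the AN-specific comparison. Nor does the uncentred test always lose power. With strong age moderation it can reject often (0.25 and 0.89 in two scenarios at f = 0.25, against 0.99 centred), but it is then testing a different quantity.

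The reply does not remove the point. The article commits to covariates, to SPSS and to possible interpretation of main effects within one family of models, and the software uses covariates as supplied. Direct execution therefore gives an uninformative main-effect test.

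**Conclusion.** The point holds as a free improvement limited to session/time main effects: habituation across the four sessions and overall pre-post change. It is not an error in the stated design, and it does not touch the primary comparison.

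If covariates are entered as collected, the standard error of these effects is inflated about 5- to 8-fold, power for a 0.5 SD decline drops from about 0.9 to about 0.06–0.10, and partial η² is understated. If habituation varies with age, the test addresses the wrong quantity and may point the wrong way. No passage suggests such age dependence, so that last consequence is conditional.

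The exact figures rest on assumed means, SDs and effect sizes. The direction does not, because ages of 10 to 21 put zero far outside the data.

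**What to change.** Add one sentence to Data Analysis, applying to every repeated-measures ANCOVA: continuous covariates are grand-mean centred in the analysed sample before entry. Alternatively, state that session/time main effects and their partial η² come from the covariate-free model, with covariates used only for the group and group × time tests. Either choice takes about one line of syntax, leaves every group × time result as it is, and needs no additional data or participants.
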